#### Pain frequency

The BBSIP will be used to assess the intensity and frequency of sensations, including pain, tightness and discomfort, in addition to health-related quality of life attributes which are specific to individuals with burn scars. The BBSIP provides unique insight into health-related quality of life in children with burn scarring, in addition to the concerns of parents/caregivers of children with burn scaring. It has been shown to have preliminary content validity, and further research is currently being conducted in children, adults and parents/caregivers of children with burn scars [57].

#### Itch

The Toronto Paediatric Itch Scale (TPIS) will be used to assess pruritus in patients younger than 5 years of age. The TPIS is a behaviour-anchored post-burn itch scale which has been demonstrated in the literature to be a valid and reliable measurement tool with a moderate inter-observer agreement (Cohen’s kappa of 0.52, *p <* 0.001) [58]. Parents/caregivers of patients younger than 5 years old will complete the TPIS, which rates itch behaviours on a scale of 0 (indicating absence of itch) to 3 (which represents severe itch with significant disruption). In addition to the aforementioned factors, this scale was selected because it has been shown to be user-friendly, intuitive and reliable for use in infants and children as young as 5 years old or less [58]. Participants 5 years of age and older will self-report their itch intensity using a 0–10 NRS. In addition, all caregivers will complete the itch component of the BBSIP. Itch will be assessed at the first COD and each follow-up until the wound is deemed re-epithelised, and it will also be assessed at 3- and 6-month reviews.

#### Health-related quality of life

The CHU9D is a generic preference-based instrument designed for use in children and adolescents to assess how their health affects their life. The CHU9D will be used to measure health-related quality of life in a way that is suitable for use in cost-utility analyses. Dimensions of the CHU9D include worry, sadness, pain, fatigue, annoyance, schoolwork/homework, sleep, daily routine and ability to partake in activities. Preference weights applied to these nine attributes enable the calculation of a multi-attribute utility score where 0 represents death and 1 represents full health [59]. The CHU9D has been developed and validated for young people aged between 7 and 17 years, and it has been shown to have good construct validity within an Australian adolescent population [60]. At each 3- and 6-month post-burn follow-up, children will self-complete the CHU9D as appropriate, and a parent/caregiver proxy-report will be completed for all participants (children of all ages).

#### Stress and anxiety

Stress is a secondary outcome and will be quantified via salivary cortisol and α-amylase. Salivary cortisol is often used as a biomarker to assess stress response and is considered to be a reliable index of hypothalamic-pituitary-adrenal axis activity [61]. The measurement of cortisol levels in saliva is the preferred method of assessment for researchers, particularly in a paediatric population; salivary analysis is non-invasive and pain-free in comparison to blood sampling and therefore does not induce additional stress and trauma (and potentially higher cortisol) as occurs with serum sampling [62]. Moreover, there is a strong correlation between cortisol levels in saliva and unbound cortisol in plasma [63]. Salivary α-amylase is also said to be a reliable, valid and sensitive biomarker for stress-related changes in the autonomic nervous system and is a proxy for noradrenaline, which is a sign of sympathetic adrenomedullary system activation [64].

Participants will place a SalivaBio Oral Swab™ (Salimetrics Europe Ltd., Newmarket, UK) under their tongue for 2 min for saliva collection. Salivary stress biomarkers will be collected at the following time points:At first presentation to the DEM or burns OPD subsequent to the application of either Burnaid® hydrogel dressings or plastic wrapImmediately after the removal of the Burnaid® or plastic wrap dressingBefore application of silver dressingsImmediately after the application of silver dressingsImmediately before premedication prior to the patient’s first CODImmediately before and after silver dressing removalAfter application of the new silver dressingsThree months after burn injury to obtain a baseline

Parents/caregivers and patients (where appropriate) will also complete a saliva collection survey which documents variables pertinent to salivary analysis. Such variables include all medications given to the patient, time the patient last woke up, time the patient last brushed their teeth, all food/drink/gum consumed by the patient during the previous hour, time the participant last consumed caffeine, pertinent smoking/tobacco history, and sample collection time. The date, time and volume of saliva collection will be recorded in the laboratory, and samples will be refrigerated at 4 °C and processed within 3 days of collection. Samples will be spun in a centrifuge at 1400 × *g* at room temperature for 15 min, and the saliva will be frozen at − 80 °C until analysis. Salivary cortisol and α-amylase will be quantified using enzyme-linked immunosorbent assay kits (Stratech Scientific, Ely, UK), with saliva samples analysed in triplicate to ensure accurate results.

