**Fig. 2 Fig2:**
[figure not shown]
SPIRIT figure. SPIRIT schedule of study recruitment, intervention and assessments. Allocation to the intervention group will occur in the Department of Emergency at Lady Cilento Children’s Hospital upon patient admission following a thermal burn injury; t1 = 3–5 days after burn injury and each subsequent dressing change; t2 = 3 months after burn injury; t3 = 6 months after burn injury

Following patient enrolment and randomisation, acute measures will be collected in LCCH DEM. Acute measures will include pain (measured using the Faces Pain Scale–Revised [FPS-R]; Face, Legs, Activity, Cry, Consolability scale [FLACC]; and visual analogue scale [VAS]), pulse rate, temperature, respiratory rate, and salivary cortisol and α-amylase, which will be recorded by the primary investigator. Acute measures will be collected before and after the application of the randomised dressing and before and after silver dressing application from the child, parent/guardian, and nursing staff. In addition, peak FLACC scores during wound cleaning and debridement will be documented, as will all analgesia and distraction techniques. All participants will have their burn wounds photographed using 3D imaging after wound debridement in the DEM to assess burn area. Patients (where appropriate) and parents/caregivers will be sent home with a diary to record pain scores and medications required prior to their first change of dressing (COD), which will typically occur 3 days after injury. Participants and parents/caregivers will be asked to bring this home diary with them to their first dressing change in the burns OPD.

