Data collection in the burns OPD will continue through to the child’s treating clinician classifying the burn wound as 95% re-epithelialised. Measures collected in the burns OPD at each dressing change appointment will include pain (measured using FPS-R, FLACC, and VAS), pulse rate, temperature, respiratory rate, and salivary cortisol and α-amylase at each dressing change appointment. These measures will be collected before and after silver dressing removal and before and after the application of new silver dressings (*see* Fig. 4). Anxiety and itch will also be assessed at each COD appointment. At the first COD appointment, all participants will have their burn wound scanned using a non-invasive treatment referred to as laser Doppler imaging to measure burn depth and vascularity of the affected area. In addition, all participants will have a 3D image of their burn taken at each COD to assess the area of the wound and its rate of re-epithelialisation.

Following wound re-epithelialisation and discharge from the burns OPD, scar outcome will be assessed at 3 and 6 months post-burn for all participants. At each 3- and 6-month follow-up, patients will have their burn wounds scanned using ultrasound to assess scar thickness; 3D imaging to assess scar area; DSM ColorMeter (Cortex Technology, Hadsund, Denmark) to examine scar colour and pigmentation; and Patient and Observer Scar Assessment Scale (POSAS), Brisbane Burn Scar Impact Profile (BBSIP) and Child Health Utility 9D Index (CHU9D) to measure health-related quality of life. Thy will also undergo itch assessment, and saliva samples will be collected to examine baseline cortisol and α-amylase levels.

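### The saliva schedule lists no sample before the randomised dressing, although the data collection section says one is taken; the sections also disagree on the 6-month sample

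*Protocol article*

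**What the plan says.** The Stress and anxiety section of the protocol article gives the outcome its status: "Stress is a secondary outcome and will be quantified via salivary cortisol and α-amylase".

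Two parts of the article set the sampling times.

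- **Data collection.** The acute measures include pain scores and "pulse rate, temperature, respiratory rate, and salivary cortisol and α-amylase, which will be recorded by the primary investigator". Their timing follows in the next sentence: "Acute measures will be collected before and after the application of the randomised dressing and before and after silver dressing application". For the late visits the section opens with "At each 3- and 6-month follow-up, patients will have their burn wounds scanned using ultrasound" and ends the same list of procedures by stating that "saliva samples will be collected to examine baseline cortisol and α-amylase levels".
- **Stress and anxiety.** This is the only list specific to saliva. Its first point is "At first presentation to the DEM or burns OPD subsequent to the application of either" of the two study dressings. The next is on removal of that dressing, followed by points around the silver dressing, points at dressing changes, and one sample three months after the burn, which is the only one the list calls a baseline.

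The Data analysis section plans comparisons between arms and within arms over time. It names no covariates for the salivary outcomes.

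**The concern.** The same item is scheduled in two incompatible ways. One section requires a swab before the randomised dressing. The other, which is the list that someone collecting saliva would naturally follow, has none. An acute sample that is not taken cannot be recovered later.

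Application of the randomised dressing is the point at which the arms begin to differ. Without a value just before it, the trial cannot describe how stress changed when the dressing went on, cannot check whether the arms started level on stress, and cannot adjust for the starting level. The article itself has families record medications, waking time, food, caffeine and collection time with the saliva, so it expects much variation that has nothing to do with the dressing. A pre-dressing value from the same child is the natural control for part of that variation.

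The word baseline adds to the confusion. A sample at 3 months is taken after randomisation and treatment, so whatever its purpose, it is not a pre-treatment value.

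**Working it through.** **1. The two schedules side by side**

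| Time point | Data collection | Stress and anxiety |
|---|---|---|
| Before the randomised dressing | Yes | Not listed |
| After it is applied | Yes | Yes (first sample) |
| After it is removed | Not stated separately | Yes |
| Before and after the silver dressing | Yes | Yes |
| Dressing changes | At each change | Pre-medication sample tied to the first change; removal and re-application points not limited to any one change |
| 3 months | Yes | Yes, called baseline |
| 6 months | Yes, called baseline | Not listed |

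Two rows conflict outright. Before the randomised dressing, Data collection requires 1 sample and the saliva list has 0. At 6 months, Data collection takes a sample and the saliva list does not.

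**2. What can still be estimated under the saliva list**

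- Difference between arms in levels after application and after removal: yes. Randomisation protects this comparison without a baseline.
- Change while the dressing is worn (at least 20 min under Treatments): yes. The post-application and post-removal samples bracket it.
- Change from before to after application: no.
- Baseline balance and baseline adjustment: no.

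**3. Precision forgone**

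The article states no figure for the salivary outcomes, so there is none to reproduce. As an illustration, let r be the correlation between a pre-dressing value and the post-dressing outcome. The article does not give r; 0.3 to 0.7 is an assumption. Adjusting for the pre-dressing value multiplies residual variance by 1 − r². With n = 29 per arm (from Sample size, assuming all 29 give usable saliva), two-sided α of 0.05 and power of 0.8, the detectable standardised difference by the normal approximation is

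(1.96 + 0.84) × √(2/29) × √(1 − r²) ≈ 0.736 × √(1 − r²).

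| Assumed r | 1 − r² | Variance reduction | Detectable standardised difference |
|---|---|---|---|
| No adjustment | 1.00 | 0% | 0.74 |
| 0.3 | 0.91 | 9% | 0.70 |
| 0.5 | 0.75 | 25% | 0.64 |
| 0.7 | 0.51 | 49% | 0.53 |

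**The case against.** The best reply is that this is a slip of wording. The list places first presentation after a dressing that is applied only once consent, stratification and randomisation are done, which is odd in itself, and Data collection plainly says "Acute measures will be collected before and after the application of the randomised dressing". Figures 2 to 4, including the schedule of assessments, are not shown here and may settle the matter. This stands as a reason not to claim that the trial omits a pre-treatment stress measure by design, which a reader might infer from the list alone. It does not remove the conflict: the article gives two incompatible instructions, and a slip in a list that staff follow has the same effect as a decision.

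Other strong readings are tempting and are not supported:

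- *Change over the dressing period cannot be estimated.* It can, from application to removal. Only change from before application is lost.
- *The saliva list covers the first dressing change only.* One entry names the first change. Those that follow carry no such limit and can be read consistently with sampling at every change.
- *The 3-month value is to be used as a baseline covariate.* Nowhere does the article propose this. The sample reads naturally as a resting level away from the acute injury, and the objection to it is one of labelling.
- *Precision falls by a known amount.* The size rests wholly on an assumed correlation, and at r = 0.3 the gain from adjustment is only 9%.

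It is also true that the primary outcome, nurse-rated FLACC after dressing application, is untouched, and that pain is assessed before the dressing.

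**Conclusion.** The contradiction is real and should be resolved, but its reach is limited. If the saliva list is followed, no child has a pre-treatment cortisol or α-amylase value. The trial then loses pre-to-post change across application, the balance check and baseline adjustment for one secondary outcome. The validity of the randomised comparison of post-dressing levels is not in question.

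The cost in precision is anywhere from small to substantial: a 9% to 49% reduction in residual variance forgone for assumed correlations of 0.3 to 0.7. If Data collection is followed instead, nothing is lost and only the list needs correcting.

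The 3-month versus 3- and 6-month mismatch is a separate, smaller inconsistency that does not touch the acute comparison. These conclusions rest on the text alone, since the figures could not be checked.

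**What to change.** 1. In the list under Stress and anxiety, add a saliva sample before the randomised dressing is applied, in line with Data collection. Keep the post-application and post-removal samples.
2. State that the pre-dressing value is the baseline covariate in the models for salivary cortisol and α-amylase.
3. Describe the 3-month sample as a resting reference taken after randomisation, not as a pre-treatment baseline, and do not use it as a covariate.
4. Make Data collection and Stress and anxiety agree on whether saliva is also taken at 6 months, and check both against the schedule figure.

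The cost is a wording change and, at most, one 2-minute swab per child that Data collection already commits to, at a point when the other acute measures are being taken anyway.

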#### Healthcare resources and costs

Healthcare resource use will be collected from the perspective of a health service provider and costed at market rates using methods that have previously been employed in trials by members of this research team at this participating centre [65, 66]. This includes recording trial intervention-related resource use (e.g., the types and amounts of acute wound dressings used) as well as other burn-related healthcare resources that may be important to a health service when deciding which of the interventions to implement in clinical services providing care for children with acute burns. Clinician labour time will be recorded for each participant and costed at state award rates for each respective discipline.

#### Blinding

Owing to the nature of the trial, blinding will not be possible, because treating clinicians, nursing staff, patients and their families will be aware of the intervention. The primary investigator will be present when the acute wound dressings are being applied and removed to obtain pain scores and additional measures from the participant, caregiver and nursing staff. The acute wound covering applied to each participant cannot be masked within this environment, and therefore investigator blinding will not be possible. In order to incorporate an element of blinding in the trial, an expert panel of burn wound specialist will conduct a blinded review of 3D photographs for all participants to assess burn wound depth and re-epithelialisation at each dressing change until complete wound healing. Wherever possible during data collection analysis, treatment groups will be de-identified.

#### Adverse effects

The proposed intervention is considered to be part of standard pre-hospital care and is currently used by Queensland Ambulance Services, despite Burnaid® products not being used at the LCCH DEM and burns OPD. Therefore, minimal adverse events are expected. Known potential adverse events (such as hypothermia, infection, haematoma, excessive exudates, unpleasant sensations, allergic reactions, chondritis, and disruption of the skin on dressing removal) have a standardised management protocol at LCCH DEM and burns OPD. In addition, children with known adverse reactions to hydrogels will be excluded from the trial. Adverse effects of the hydrogel dressing will be monitored by reviewing patient medical records and via self-report data from parents/caregivers, participants (where appropriate), and treating clinicians. All adverse events will be reported to the clinical health service and the overseeing HREC. If a consultant believes that Burnaid® hydrogel dressings were not appropriate for a patient’s treatment, discontinuation or alteration of treatment will be at their discretion, and data collection for such participants will cease from that time point.

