#### Control

Plastic wrap is the current acute wound covering applied to thermal burn injuries at LCCH, and it will serve as the control arm in this trial. Participants randomised to receive plastic wrap will have the dressing applied after first aid and will have the dressing remain on for a minimum of 20 min, followed by standard burn care.

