### Sample size

The sample size estimate was calculated on the basis of the primary outcome of pain intensity after dressing application. Previous researchers assessing paediatric burn pain reported that pain scores within each subject group were normally distributed with an SD of 2.4 [37]. To detect a significant between-group difference of 1.8 in pain scores after dressing application, 29 experimental participants and 29 control participants will need to be recruited in order to reject the null hypothesis that the population means of the experimental and control groups are equal with probability (power) of 0.8. The type I error probability associated with the test of this null hypothesis is 0.05. With up to a potential 20% loss to follow-up, the calculated target sample size is equal to 72 participants. LCCH treats approximately 25–34 children per month in the DEM for acute burn injury. On the basis of these estimates and a historical 70% success rate for trial recruitment within LCCH, it is predicted that around 17 patients will be recruited per month. Therefore, it is estimated that data collection should be completed within 12 months from recruitment commencement.

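### The stated search for adverse effects covers the hydrogel dressing only, so adverse-event counts would not be comparable between the two arms

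*Protocol article*

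**What the plan says.** Collection of harms is described in one place, the Adverse effects section of the protocol article. It makes four relevant statements.

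- **How events are found:** "Adverse effects of the hydrogel dressing will be monitored by reviewing patient medical records and via self-report data", supplied by caregivers, participants where appropriate, and treating clinicians.
- **Where events are sent:** "All adverse events will be reported to the clinical health service and the overseeing HREC". No arm is named.
- **How known events are handled:** they "have a standardised management protocol at LCCH DEM and burns OPD". No arm is named.
- **When data collection ends early:** "If a consultant believes that Burnaid® hydrogel dressings were not appropriate for a patient’s treatment", treatment may be stopped or altered at the consultant's discretion, and data collection for that child ends there. Only Burnaid is named.

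The Control section says of plastic wrap that "it will serve as the control arm in this trial" and is silent on adverse events. The Blinding section says that "treating clinicians, nursing staff, patients and their families will be aware of the intervention".

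**The concern.** The article is not merely silent. It states a method of finding harms and ties it to one arm. Several of the events it lists are not specific to a hydrogel: infection, hypothermia, and disruption of the skin when a dressing comes off could follow from the burn itself or from either covering. The First aid section gives prevention of hypothermia as one reason for covering a burn after cooling, so that risk exists whichever dressing is used. Only a control count gathered in the same way can separate background from dressing effect.

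The decision that follows makes this matter. The abstract says that Burnaid will become standard practice in the emergency department if it reduces pain. The Adverse effects section says that these products are not currently used there or in the burns outpatient clinic. The First aid section reports no studies of these dressings in children with burns. The randomised contrast would therefore be useful for safety as well as for pain. Because the people supplying reports know the allocation, unequal searching would add to any difference in their readiness to report.

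**Working it through.** The article states no adverse-event figure, so there is none to reproduce. The check compares the text by arm and then shows why the size of any bias stays open.

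**Step 1: what is specified for each arm**

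| Element | Burnaid | Plastic wrap |
|---|---|---|
| Record review for adverse effects | Stated | Not stated |
| Adverse-effect reports from caregivers, children, clinicians | Stated | Not stated |
| Onward reporting of all adverse events | Stated | Stated (no arm named) |
| Management protocol for known events | Stated | Stated (no arm named) |
| Data collection ends if dressing judged inappropriate | Stated | Not stated |

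The third and fourth rows deal with events already identified. They do not say how events are looked for. The first two rows do, and they differ by arm.

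**Step 2: related data collected in both arms**

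- Data collection: temperature before and after the randomised dressing, and again at dressing changes.
- Data collection and Days to re-epithelialisation: 3D wound images at first presentation and at each dressing change, with blinded panel review.
- Staff and caregiver perspectives on dressings: ratings of application, removal and comfort.
- Blinding: the primary investigator is present when the acute dressings are applied and removed.
- Data collection: chart and parent information on mechanism, burn area, first aid, transport and time to presentation.

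These bear on some harms, chiefly hypothermia and discomfort. None is described as adverse-event collection. The panel's stated task is depth and re-epithelialisation, and the chart items are baseline details.

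**Step 3: what unequal capture would do (assumed values)**

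Let the true event risk be *p* in both arms, with 36 children per arm (abstract). Let *b* be the share of events captured under Burnaid and *s* the share captured under plastic wrap.

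- Expected counts: 36·*p*·*b* for Burnaid and 36·*p*·*s* for plastic wrap.
- Apparent risk ratio: *b*/*s*. It does not depend on *p*.

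Example with *p* = 10%, *b* = 1, *s* = 0.5: 36 × 0.10 = 3.6 events against 36 × 0.10 × 0.5 = 1.8, a ratio of 2.0 with no true difference.

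| *b* | *s* | Apparent ratio |
|---|---|---|
| 1 | 1 | 1.0 |
| 1 | 0.75 | 1.33 |
| 1 | 0.5 | 2.0 |
| 1 | 0.25 | 4.0 |
| 0.75 | 1 | 0.75 |

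The last row represents Burnaid events lost because data collection stopped early. Nothing in the article fixes *b* or *s*. The table shows that the ratio can fall on either side of 1, and nothing more.

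**The case against.** The case against has four parts.

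- **A condensed article.** Adverse-event forms and tables by arm are commonly left to the full protocol. That excuses silence, and the absence of such detail is not the point here. The point is a sentence that is present and names one arm. If the full protocol already searches both arms, the article's sentence simply needs correcting.
- **Reporting all events presupposes recording them.** This stands in part. A reader might infer that no plastic-wrap events would be recorded at all, and the text does not support that. The reporting sentence is not limited by arm, and the shared measurements would bring some control events to light. It still does not set up the same search.
- **Active versus passive.** A reader might infer that Burnaid families are actively questioned while controls are left to volunteer events. The article says neither. It speaks of self-report data for one arm and gives no method for the other.
- **No safety comparison is promised.** This stands. Safety is not a listed primary or secondary outcome, few events are expected, and the stated condition for adoption is pain reduction. The consequence is confined to how any adverse-event counts can be read.

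**Conclusion.** The point holds as a defect of stated wording. The only method given for finding adverse effects is limited to the hydrogel dressing, and no section extends it to plastic wrap. Followed as written in an unblinded trial, the two arms' counts would not be comparable, and non-specific events could not be assigned to Burnaid or to the burn.

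Its size cannot be stated. It is tempting to say that the plan biases safety against Burnaid, perhaps twofold. The ratio of 2.0 rests wholly on an assumed 50% capture in controls. The Burnaid-only provision that ends data collection could pull the other way, so even the net direction is open. The primary pain outcome, the sample size and the randomisation are untouched. Equal collection would still leave 36 children per arm, too few to say much about uncommon events, but the counts could then be compared.

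**What to change.** Replace the ascertainment sentence with:

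*Adverse events will be collected in both arms by the same medical-record review and the same self-report sources, at the same visits, and reported by randomised arm.*

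The Burnaid-only provision under which data collection ends must be reconciled with that sentence as far as collecting adverse events is concerned. No view is taken here on the clinical decision to stop or alter a dressing.

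The cost is a little extra chart review and data entry for the 36 control children, who already attend the same visits. Sample size and the primary analysis do not change.

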### Primary outcome measure

The primary outcome of this trial is pain intensity after acute dressing application (*see* Measure 2 in Fig. 3). Observational reports from nursing staff using the FLACC scale will be used to measure this primary study outcome for all participants enrolled in this trial.

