### Data analysis

The data set will be analysed using IBM SPSS Statistics software (version 22; IBM, Armonk, NY, USA) and Stata software (StataCorp, College Station, TX, USA). Descriptive statistics will be calculated for all outcomes. Univariate parametric analyses (e.g., *t* test, chi-square test) or alternative non-parametric equivalent tests (e.g., Mann-Whitney *U* test) will be used to assess differences between groups at baseline where appropriate. Between-group differences in outcomes will be analysed using regression models. When analyses include multiple measures on the same participant, mixed effects methods will be used to account for probable non-independence in observations. When outcomes are on an interval scale, linear models will be used. When outcomes are binary, logistic models will be used, and when outcomes are recorded as count data, Poisson models will be used. Sensitivity analyses will be undertaken using multiple imputation methods, where it can be assumed data are missing at random. Analysis of differences between groups, and also differences within groups over time, will be undertaken. Analyses will be done on an intention-to-treat basis. Significance will be set at *p* < 0.05.

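### Stopping data collection when a consultant judges Burnaid unsuitable contradicts the stated intention-to-treat analysis and removes later outcomes from the Burnaid arm

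*Protocol article*

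**What the plan says.** The Adverse effects section of the protocol article sets the rule. Where a consultant thinks Burnaid was unsuitable for a child, "discontinuation or alteration of treatment will be at their discretion, and data collection for such participants will cease from that time point". The rule names Burnaid only. The Control section and the rest of the article state no equivalent for plastic wrap.

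The same section lists the events it has in mind: "hypothermia, infection, haematoma, excessive exudates, unpleasant sensations, allergic reactions, chondritis, and disruption of the skin on dressing removal". It does not say which of these, if any, would lead a consultant to stop the dressing.

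The Blinding section says that "blinding will not be possible, because treating clinicians, nursing staff, patients and their families will be aware of the intervention".

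The Data analysis section says "Analyses will be done on an intention-to-treat basis", and on missing data: "Sensitivity analyses will be undertaken using multiple imputation methods, where it can be assumed data are missing at random".

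On the primary endpoint: "The primary outcome of this trial is pain intensity after acute dressing application". It is the nurse-rated FLACC score, labelled Measure 2 in Fig. 3, which is not reproduced in the text available.

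**The concern.** Intention-to-treat analysis compares the arms as randomised. That requires outcomes from every randomised child, including those whose dressing was changed. The Adverse effects section instructs staff not to collect those outcomes. This is an affirmative instruction and not a detail left to a fuller document, and no later analysis plan can recover data that were never collected.

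Three features make the loss more than a loss of precision. It arises in one arm only, as far as this rule goes. It is triggered by a clinician who knows the allocation. And it depends on a judgement about how the allocated dressing suits the child, which may be related to that child's pain or healing. If it is, the children left in the Burnaid arm are no longer comparable with the control arm, and an analysis that assumes the data are missing at random does not clearly repair this.

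**Working it through.** **Setting the sections side by side**

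- Adverse effects: follow-up ends at the consultant's decision, in Burnaid children.
- Data analysis: all randomised children are analysed as randomised.
- Data collection: clinic measures run until the wound is classed as 95% re-epithelialised, and scar assessment at 3 and 6 months is planned for every participant.

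The first cannot be carried out together with the other two for an affected child.

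**What is lost**

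- Lost for certain, if scheduled after the decision: peak FLACC during cleaning and debridement, pain around silver dressing application and at dressing changes, days to re-epithelialisation (the article's second hypothesis), and scar and quality-of-life measures at 3 and 6 months.
- Lost conditionally: the primary FLACC score. Data stop only from the decision onward, so a score already recorded is kept. The dressing stays on for at least 20 min, so an earlier decision is possible, but the exact time of Measure 2 is in the figure.

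**The plan's own figure**

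Inputs from the Sample size section: difference 1.8, SD 2.4, power 0.80, type I error 0.05 (taken as two-sided), 20% loss, total 72.

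n per arm = 2 × (1.960 + 0.842)² × (2.4 / 1.8)² = 2 × 7.85 × 1.778 = 27.9, so 28 by the normal approximation. The exact t-test calculation gives 28.9, so 29, as stated. Allowing for 20% loss, 58 / 0.8 = 72.5, against the stated 72, which is 36 per arm. The stated figure is reproduced to within rounding.

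**Illustration of size for the primary outcome**

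Assumptions, none of them from the documents: k Burnaid children are lost, all before Measure 2; scores are normal; there is no true difference; and the remaining children are compared by a two-sample t test. There are 36 per arm with SD 2.4, simulated 40,000 times. Monte Carlo error on the bias is about 2.4 × √(2/36) / √40,000 = 0.003 points. With k = 0 the simulated type I error was 0.049.

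| k lost of 36 | Stopping unrelated to pain: bias (power at 1.8) | Correlation 0.5 with pain: bias, type I error | Highest scorers always lost: bias, type I error |
|---|---|---|---|
| 1 (2.8%) | 0 (0.876) | 0.07, 0.052 | 0.14, 0.064 |
| 2 (5.6%) | 0 (0.871) | 0.13, 0.057 | 0.27, 0.086 |
| 4 (11.1%) | 0 (0.860) | 0.24, 0.071 | 0.49, 0.155 |
| 7 (19.4%) | 0 (0.841) | 0.40, 0.107 | 0.80, 0.314 |

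Bias is in FLACC points in favour of Burnaid. With nobody lost, power is 0.881. The middle column is half the right-hand one, as expected, because the bias scales with the correlation: 0.5 × 0.27 = 0.135 and 0.5 × 0.49 = 0.245. The row k = 7 is an outer bound, in which roughly the whole 20% loss allowance falls on this one rule.

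Against the design difference of 1.8, the bias for 2 to 4 children is 7% to 13% at correlation 0.5 (0.13/1.8 to 0.24/1.8), and 15% to 27% in the worst case (0.27/1.8 to 0.49/1.8).

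**The case against.** The strongest reply is that the rule may rarely be used and may seldom touch the primary endpoint. The article expects few adverse events and excludes children with known hydrogel sensitivity. Scores taken before the decision are kept. This stands, and it is why no firm size can be given for the primary comparison.

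Four stronger readings are tempting, and the documents do not support them.

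- *Children are removed because of pain.* The text says only that Burnaid was judged not appropriate. Of the eight events listed, one is plainly sensory; infection, haematoma, exudate, allergy and chondritis stand beside it. A link with pain is plausible but remains an inference.
- *The rule defeats the intention-to-treat analysis of the primary outcome.* That would require decisions before Measure 2, which the text neither states nor excludes.
- *All missing data fall in one arm.* The Recruitment section lets families in either arm withdraw at any time. The asymmetry belongs to this rule only.
- *Harms go unrecorded.* The same section provides for medical-record review and for reporting all adverse events to the health service and ethics committee, and the Recruitment section has withdrawals and discontinuations recorded.

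It can also be said that imputation is promised only where missing at random can be assumed, so the article does not claim to cover this case. That is correct, but it leaves these children with no stated remedy.

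None of this removes the contradiction or the loss of outcomes scheduled after the decision.

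**Conclusion.** The point holds as a contradiction between a stated data-collection rule and the stated analysis population. For each affected Burnaid child, outcomes after the decision are lost for a treatment-related reason decided by an unblinded clinician, and missing at random is hard to assume. The direction and size of any bias in re-epithelialisation, scar and quality of life cannot be derived from the article.

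For the primary FLACC score the effect is conditional. If 2 to 4 of 36 Burnaid children are lost before Measure 2, the bias toward Burnaid is nil if stopping is unrelated to pain, 0.13 to 0.24 points with type I error of about 6% to 7% at correlation 0.5, and 0.27 to 0.49 points with type I error of 8.6% to 15.5% if the highest scorers are always the ones lost. The number lost, the correlation and the timing are all assumed. The true effect on the primary comparison may be small.

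Severity: should be fixed. The primary result is not shown to be compromised, but the loss cannot be repaired afterwards and is cheap to prevent.

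**What to change.** Replace only the data-collection clause in the Adverse effects section, for example with:

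*Participants in either arm whose allocated dressing is stopped or changed stay in follow-up. All scheduled pain, healing, scar and quality-of-life measures are still collected unless consent for data collection is withdrawn, and these participants are analysed in the arm to which they were randomised. The time of and reason for the change are recorded in both arms.*

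The consultant's discretion over treatment is left exactly as it is. Discontinuations are already to be recorded, so time and reason are the only new items.

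The cost is a short amendment and two fields on the data collection form. The visits are already scheduled and the target of 72 does not change. The amendment helps only children whose data are collected after it takes effect, so it is best made while data collection is running.
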